## Data analysis

In this study a range of statistical tests will be used to analyse the data corresponding to the four aims. Aim 1 will use Cox proportional hazards regression to determine if the time to recovery from concussion (measured in days), differs among groups categorised by hormone profile at the point of injury (five profiles: Follicular phase, Midcycle, Luteal phase, oral contraception, IUD). Aim 2 will apply an ANOVA to compare the ratios of miR-27a-5p/miR-30a-3p expression, across these five groups. Model-estimated means and pairwise contrasts between groups will also be computed. For Aim 3, the focus is on whether self-reported symptoms, quantified both as the number of symptoms present (range 0–16) and as a total symptom burden (sum of severity scores; range 0–160), differ among hormone profile categories. These dependent variables will be analysed using ANOVA, with the five hormone profiles specified as the independent variable. Aim 4 will employ a linear mixed model to investigate changes in low energy availability across the recovery period. This model will incorporate the day of recovery and total symptom burden as fixed effects and will account for repeated measures over time by specifying participant as a random effect. The interaction between symptom burden and recovery time will also be evaluated to understand if these variables are collectively associated with low energy availability.

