## Methods/design

### Aim

The aims of this study are to: 1) determine if the time to recovery (in days) differs among groups categorised by their hormone profiles at the point of concussion injury, 2) examine whether the ratio of sncRNAs in saliva differ across groups categorised by their hormone profiles at the point of concussion injury, 3) assess whether self-reported symptoms differ among groups categorised by their hormone profiles at the point of concussion injury, and 4) investigate whether low energy availability changes across the recovery period, and if this is associated with symptoms experienced.

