#### Participants and recruitment

Females presenting to ED within three days of injury with suspected concussion are recruited by ED healthcare professionals. Participants are invited to participate if they are biologically female (self-report), of reproductive age (16–50 years) and have a confirmed diagnosis of concussion from the consulting healthcare professional. The diagnostic criteria for concussion are those outlined in the most recent international consensus statement from the concussion in sport group. [51] Participants will be excluded if they have Polycystic Ovarian Syndrome (PCOS), a pre-diagnosed psychiatric disorder or neurological condition (e.g. epilepsy, cerebral palsy) or if they have had more than three previously diagnosed concussions; these are known modifiers for prolonged recovery. [52, 53] These specific exclusion criteria will be ascertained by the consulting ED healthcare professional as part of the initial routine assessment for concussion. Full inclusion/exclusion criteria are shown in Table 1. The standard concussion assessment is detailed in Fig. 1. Study recruitment commenced February 2022, however there was interruption due to COVID related sickness and changes in the ED through November 2022. The study recommenced in January 2023 and is in progress.

**Table 1 Tab1:** Inclusion and exclusion criteria

Inclusion criteria	Exclusion criteria
Females of reproductive age: 16–50 years (with a menstrual cycle for a minimum of 2 years if naturally cycling)	Had three or more previously diagnosed concussions
Natural regular menstrual cycle 28–35 days long, or Currently taking Oral Contraceptive Pill (OCP), or Currently have Intra Uterine Device (IUD), or	Current concussion was more than 3 days ago
	Post-menopause
	Started taking medication that would alter reproductive hormone concentrations (Corticosteroids, e.g., Prednisone. Antidepressant or Antipsychotic medication) within the last 3 months
	Current clinical diagnosis of an eating disorder
	Pre-diagnosed psychiatric disorder
	Pre-diagnosed neurological condition
	Polycystic Ovarian Syndrome (PCOS)
	Oligomenorrheic (irregular periods), or
	Amenorrheic (loss of periods for 3 months or longer)
Confirmed diagnosis of concussion by a medical doctor (within 3 days of injury)	GCS^a^ score less than 15 at 4 h after initial assessment. These patients may be referred for a CT scan and will not be eligible for the study

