Participants are categorised into one of five hormone profiles as follows; 1) Follicular phase if question C1 is answered as “1 week ago”, 2) Mid-cycle if question C1 is answered “2 weeks ago”, 3) Luteal phase if question C1 is answered “3 weeks ago” or “4 weeks ago”, 4) Oligomenorrheic if C1 was answered “1–2 months ago”, “3–4 months ago” or “5 months ago or more”, 5) Using contraceptive if question 3.1a is answered “yes”.

Scoring of question 3.2 remains the same, i.e., if a participant ticks any of the boxes within the 0–4 weeks’ timeframe the same score is applied as the original question. In eumenorrheic participants this will help estimate menstrual cycle phase at point of injury. This information is used to understand any association between hormonal profile and or LEAF_Q score with symptom severity and duration of concussion.

The Brain Injury Screening Tool (BIST) is a brief screening tool for use on initial presentation after injury to guide health care pathway decision making and to monitor symptoms and recovery over time. [59] The BIST was developed in the NZ context to fit the clinical environment and to provide consistency across multiple environments and referral pathways (e.g. GP clinic, ED, Urgent Care Centres), the tool has also been psychometrically tested. There are two sections in the BIST; the first section is used to determine if there are any clinical ‘red flags’ which require referral to hospital, therefore this component is not included in this study. The second section of the BIST includes a 16-item symptom report scale for patients to rate how much they now experience the symptoms listed on a scale of 0 (not at all) to 10 (severe). Higher symptom scores are indicative of higher symptom burden. Participants are asked to complete this part of the BIST at point of presentation with injury and at seven-day time intervals throughout the study to monitor symptoms and recovery over time.

The final question asks if the participant has made a full return to work/study and how many follow-up appointments they had. The number of days between injury and full return to work/study will be used as a proxy for recovery. This question is included in the weblink sent at all timepoints (i.e., 7, 14, 21, 28 days etc.) until the participant reports they have achieved a full return to work/study, at which point participation in the study will be complete. Detail of information collected each week is included in Table 2.

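### IUD is analysed as one hormone profile in Aims 1–3, with no stated rule separating hormone-releasing from non-hormonal devices

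*Protocol article*

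**What the plan says.** The Aim section states that the first aim is to "determine if the time to recovery (in days) differs among groups categorised by their hormone profiles at the point of concussion injury". Aims 2 and 3 use the same grouping idea for the salivary RNA ratio and for symptoms.

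Three places in the protocol article bear on how an IUD user is handled:

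- **Eligibility** (Participants and recruitment, Table 1): one qualifying route is "Currently have Intra Uterine Device (IUD), or". No device type is named.
- **Classification** (Surveys and questions): five profiles are listed. Three are cycle phases taken from question C1, one is oligomenorrheic, and the last is "5) Using contraceptive if question 3.1a is answered" yes. There is no IUD class.
- **Analysis** (Data analysis): the factor is "five profiles: Follicular phase, Midcycle, Luteal phase, oral contraception, IUD". It enters the Cox model for Aim 1. For the second aim, "Aim 2 will apply an ANOVA to compare the ratios of miR-27a-5p/miR-30a-3p expression, across these five groups", with pairwise contrasts. The Aim 3 ANOVAs are run "with the five hormone profiles specified as the independent variable".

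Aim 4 does not use the factor. Nowhere is an IUD described as hormonal or non-hormonal. The limitations section mentions self-report, recall and the lack of gold-standard verification, but not device type.

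**The concern.** The factor is meant to contrast hormone states at injury. Four of its five levels in the Data analysis section can be read that way; IUD cannot. A hormone-releasing device is a progestin exposure. A non-hormonal (copper) device leaves the woman in a follicular, mid-cycle or luteal state, which are the states that three other levels are there to isolate. The document does not state this pharmacology; I take it as general knowledge.

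As written, a woman with a non-hormonal IUD is removed from the phase group that describes her and placed with women on progestin. A difference between IUD and another group would then not identify which exposure it reflects, and the phase groups would lose members. Both the primary aim and two secondary aims are affected, in a study of 38 women spread over five groups.

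**Working it through.** **1. The plan's own figure.** Inputs from Sample size calculation: hazard ratio 1.5 (log 0.4055), covariate SD 1.5, R² 0.2, event rate 0.9, power 80%, type I error 0.05 (taken as two-sided), dropout 20%.

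Events = (1.960 + 0.842)² / (1.5² × 0.4055² × (1 − 0.2)) = 26.52. Then N = 26.52 / 0.9 = 29.47, rounded up to 30, and 30 / 0.8 = 37.5, rounded up to 38. Both stated figures reproduce, and this point does not dispute them.

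**2. Why that hazard ratio cannot size this problem.** It is an effect per unit of a covariate with SD 1.5. A 0/1 indicator for IUD membership has SD √(p(1 − p)), which is at most 0.5 and is √(0.2 × 0.8) = 0.4 if one woman in five is an IUD user. The plan therefore gives no hazard ratio for an IUD contrast.

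**3. Tracing a non-hormonal IUD user through the text.**

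- Table 1 admits her.
- Under Surveys and questions, if question 3.1a covers devices she joins all contraceptive users. If it does not, she is classed by C1. The wording of 3.1a is not shown. If she answers yes to 3.1a and also gives a C1 date, she meets two profiles, and no order of precedence is stated.
- Under Data analysis she belongs to IUD, together with users of hormone-releasing devices.

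Neither section separates the device types. Adopting the Data analysis list alone would leave the IUD level mixed.

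**4. Direction of the effect.** Let c be the non-hormonal share of the IUD group, μH the expected outcome with a hormone-releasing device, μN that of naturally cycling women, and μO that of oral contraceptive users. The IUD group has expectation (1 − c)μH + cμN. This is exact for the ANOVA means and approximate for log hazards.

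- Against naturally cycling women: (1 − c)(μH − μN), which shrinks toward zero.
- Against oral contraception: (μH − μO) − c(μH − μN), which can move either way.

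The first line assumes that non-hormonal users behave like the comparator. If outcome varies by phase, they pull the IUD group toward a phase average instead.

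**5. Illustrative size.** With equal groups (assumed), there are 30/5 = 6 analysed or 38/5 = 7.6 recruited per profile. The document does not give c. The number needed for the contrast with naturally cycling women scales as 1/(1 − c)².

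| c (assumed) | Women misplaced, of 6 to 7.6 | Share of contrast left | Multiple of events or sample size |
|---|---|---|---|
| 0 | 0 | 1.00 | 1.0 |
| 0.25 | 1.5 to 1.9 | 0.75 | 1.8 |
| 0.50 | 3.0 to 3.8 | 0.50 | 4.0 |
| 0.75 | 4.5 to 5.7 | 0.25 | 16.0 |

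**The case against.** **The contrast is weak whatever is done.** If a two-group hazard ratio of 1.5 is borrowed purely as a benchmark, 6 against 6 women gives 12 × 0.9 = 10.8 events and power Φ(√10.8 / 2 × 0.4055 − 1.96) = Φ(−1.29), about 10%. Removing a few women from the IUD group does not rescue it. This stands and limits the practical gain. It does not justify a level whose meaning is unclear, because these contrasts will be estimated and read even if underpowered.

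**Device type may already be recorded.** Only the modified part of the menstrual questions is reproduced, and splitting oral contraception from IUD in the analysis implies that more than one yes/no answer is held. The Table 1 entry also ends on a conjunction, so that cell may be incomplete as read. A reader might infer that device type is not collected; the document does not establish that. What is missing is a rule that uses it.

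**It is detail for a fuller document.** This would hold if the article were silent on grouping. It is not: it fixes the eligibility routes, the assignment rule and the analysis factor.

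**The mismatch between the two profile lists is the larger defect.** This is fair. The IUD level analysed has no assignment rule at all, and device type is best settled in the same edit.

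**Unverified self-report is already disclosed.** That limitation does not reach this point: a perfectly recalled IUD answer would still mix two exposures.

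**Conclusion.** The point holds as a badly defined factor level. No stated rule keeps non-hormonal IUD users apart from progestin users in groups meant to contrast hormone states, so if both types are enrolled the IUD contrast is diluted against naturally cycling women and ambiguous as a hormone effect. This rests on two things the document does not supply: that some IUDs release no hormone (general knowledge), and that both types are present in the cohort (possible under Table 1, not shown). If every device is of one type, there is no mixing.

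Two stronger readings are tempting and are not supported. One is that the IUD group cannot be interpreted at all; the algebra shows attenuation against naturally cycling women and an uncertain direction against oral contraception. The other is that the plan's hazard ratio of 1.5 falls by a calculable amount; that figure is per unit of a covariate with SD 1.5, and the device mix is unknown. The stated sample size is unaffected. This should be corrected while recruitment is open, but it does not threaten the study as a whole.

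**What to change.** Make the change together with the reconciliation of the profile lists in Surveys and questions and in Data analysis:

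- Define the fifth profile as hormone-releasing IUD.
- Assign women with a non-hormonal IUD to follicular, mid-cycle or luteal phase from question C1, and state that this takes precedence over the contraceptive answer to question 3.1a.
- State where such a woman goes if she has no usable C1 answer, since the questionnaire skips C1 when normal menstruation is answered no or don't know.
- Take device type from existing questionnaire data if it is held there. Otherwise add one survey item and query the IUD users among the 14 women who had started by 18 August 2023.
- Leave the eligibility of enrolled women unchanged. Where a non-hormonal IUD user does not fit the natural-cycle wording in Table 1, the sponsor should reconcile the sections.

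The cost is a line or two in the classification rule, at most one survey item, and a short query. A sixth profile is not advisable: 30/6 is 5 analysed women per group under equal allocation. The downside is a smaller IUD group, which may have to be described rather than tested.

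### The hormone-profile exposure for Aims 1–3 has two incompatible definitions, and the stated classification rule cannot produce the groups that are analysed

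*Protocol article*

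**What the plan says.** **Classification (Protocol article, Surveys and questions).** The rule opens "Participants are categorised into one of five hormone profiles as follows; 1) Follicular phase if question C1 is answered as" one week ago. Two weeks gives mid-cycle, and three or four weeks gives luteal. The fourth profile is "4) Oligomenorrheic if C1 was answered" with any of the three options from one to two months upward. The last is "5) Using contraceptive if question 3.1a is answered" yes.

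**Analysis (Protocol article, Data analysis).** Aim 1 compares "five profiles: Follicular phase, Midcycle, Luteal phase, oral contraception, IUD". Aim 2 runs an ANOVA "across these five groups", and Aim 3 runs ANOVAs "with the five hormone profiles specified as the independent variable".

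**Eligibility (Protocol article, Participants and recruitment, Table 1).** The inclusion column admits women with a "Natural regular menstrual cycle 28–35 days long", pill users and IUD users. The exclusion column, as printed, contains "Oligomenorrheic (irregular periods), or", followed by amenorrhoea of three months or longer.

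**Timing.** The aims define the profile at the point of injury. The questionnaire that contains C1 is first completed seven days after initial assessment.

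**The concern.** Hormone profile is the exposure in the primary Cox model and the grouping factor in the Aim 2 and Aim 3 ANOVAs. The article gives two five-group lists for it, and they are different groups. Which list is used decides group membership and every contrast; with Table 1 as printed, it also decides the degrees of freedom. While both stand, the choice between them could be made once outcomes are known. This is a conflict between two explicit statements, so it is not a detail that a condensed article simply leaves to a fuller document.

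**Working it through.** **1. The two lists side by side.**

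| Profile | Classification rule | Data analysis |
|---|---|---|
| Follicular | yes | yes |
| Mid-cycle | yes | yes |
| Luteal | yes | yes |
| Oligomenorrheic | yes | no |
| Using contraceptive (undivided) | yes | no |
| Oral contraception | no | yes |
| IUD | no | yes |

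Three of five labels are shared. The contraceptive profile rests on one yes answer, so no set of answers under the rule returns oral contraception or IUD as separate groups.

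**2. Is the rule mutually exclusive and complete?** The first four profiles depend only on C1, and the fifth only on item 3.1a. C1 has seven answers, plus the case where it is skipped because normal menstruation was answered no or don't know. Crossing these with contraceptive use (yes or no) gives 8 × 2 = 16 combinations:

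- one profile: 8 (seven C1 answers without contraception, and contraception with C1 skipped);
- two profiles: 7 (contraception with any C1 answer);
- no profile: 1 (no contraception and C1 skipped).

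These are counts of answer patterns, not of women.

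**3. Degrees of freedom.** The analysis list has five groups, so 5 − 1 = 4. With the oligomenorrheic profile empty, as Table 1 is printed, the classification rule leaves four groups, so 4 − 1 = 3. If those women are in fact eligible, the rule gives five groups and 4 degrees of freedom, but two of the five are not the analysed ones.

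**4. Group size.** The plan's own figure reproduces. Events = (1.960 + 0.842)² / (1.5² × 0.4055² × (1 − 0.2)) = 26.5; 26.5 / 0.9 = 29.5, rounded up to 30; 30 / 0.8 = 37.5, rounded up to 38. The arithmetic of the sample size is not in question here. With equal groups, 38 / 5 = 7.6 women each. Moving two women changes a group by 2 / 7.6 = 26%, and moving three by 3 / 7.6 = 39%.

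**5. Regular women past day 28 when surveyed.** C1 steps from four weeks to one to two months, and the latter carries the oligomenorrheic label. If every day after 28 falls in that option, the share of the cycle affected is (L − 28) / L for cycle length L:

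- L = 35: 7 / 35 = 20%;
- L = 32: 4 / 32 = 12.5%;
- L = 30: 2 / 30 = 6.7%;
- L = 28: 0.

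If women choose that option only after 30 or 31 days, the 35-day figure falls to 5 / 35 = 14% or 4 / 35 = 11%.

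**6. Survey date against injury date.** C1 is first asked seven days after assessment. Enrolment is allowed up to three days after injury, so the lag is about 7 to 10 days. Assume that the cycle day at injury is uniform, that each weekly option covers exactly seven days, that days past 28 are labelled oligomenorrheic, and that answers are not referred back. The label at survey then differs from the label at injury on 21 of 28 days (75%, lag 7) or 24 of 28 (86%, lag 10) for a 28-day cycle, and on 28 of 35 (80%) or 31 of 35 (89%) for a 35-day cycle. The article says that C1 helps to estimate phase at injury but states no back-calculation, so these figures show what happens only if none is made.

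**The case against.** The strongest reply is that the Data analysis section fixes one list and uses it for all three aims, and that this list matches the eligible strata in Table 1. Pill and IUD use are separate eligibility items, so the split could come from screening. The rule places each woman in one profile and ties the C1 detail to eumenorrheic women, so letting contraceptive use override C1 is a natural reading. This stands in part. A reader might infer that the exposure cannot be derived at all, and the document does not support that. It does not state either step, however, and it states a different rule.

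Three further inferences go too far:

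- **That the oligomenorrheic group is certainly an excluded population and must be empty.** The IUD entry in the inclusion column ends in a dangling connector, and the oligomenorrheic row ends in the same style, so the table may have been displaced in extraction. The conflict survives either reading, because the analysis has no group for these women.
- **That 20% of regular women are mislabelled.** That is the longest eligible cycle with the strictest cut. It also applies to the survey day: a regular woman injured on days 29–35 would usually have had another period before answering C1.
- **That IUD type is not recorded.** Item 3.1 is not reproduced, so this cannot be checked. Whether hormone-releasing and non-hormonal devices should be separated is secondary and cannot be settled from this document.

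The limitations section acknowledges self-report and recall, but not the conflicting lists.

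**Conclusion.** The point holds, and it should be fixed before analysis. The exposure for the primary aim and for Aims 2 and 3 has two incompatible definitions that share three of five labels. The stated rule cannot return two of the analysed groups, assigns one group that the analysis lacks, and gives two profiles for 7 of 16 answer patterns and none for 1. These results come from the text alone and need no assumption.

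The sizes are conditional. The change from 4 to 3 degrees of freedom assumes Table 1 as printed. The 26–39% change in a group assumes 38 women in equal groups. The 20% is an upper bound. The 75–89% relabelling assumes that answers are not referred back to the injury date. The contradiction is repairable, because the eligibility information distinguishes pill from IUD use.

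**What to change.** State one ordered, mutually exclusive derivation and use it word for word in Surveys and questions and in Data analysis:

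1. Contraceptive use takes precedence over C1, with users split into pill and IUD from the eligibility information.
2. Among non-users, cycle phase is referred back to the injury date, and a regular woman still within her usual cycle length is not labelled oligomenorrheic.
3. The oligomenorrheic profile is reconciled across the classification rule, Table 1 and the analysis list so that all three agree. The investigators must settle which is intended. Any woman who fits no analysed group is reported separately.

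The cost is wording plus three data items: contraceptive type, last-period date and usual cycle length. Contraceptive type alone is not enough, because weekly options do not give the cycle day at injury. Fourteen women had started by 18 August 2023. For women already enrolled, the extra items may have to be requested, or cycle day approximated from the weekly options, with the approximation reported.

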**Discussion:**

If saliva samples confirm presence of sncRNAs in females with concussion, it will provide evidence of the potential of saliva sampling as an objective tool to aid in diagnosis of, and confirmation of recovery from, concussion. Findings will determine whether expression of sncRNAs is influenced by steroid hormones in females and may outline the need for sex specific application and interpretation of sncRNAs as a clinical and/or research tool.

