#### sncRNA (miRNA) expression analysis

The sncRNA targets from saliva will be extracted using the MagMAX mirVana total RNA isolation kit (A27828, Thermo Fisher Scientific, Waltham, Massachusetts, US) using manufacturer’s instruction with modification for saliva extraction. After isolation of total RNA (including snc/miRNA), these will undergo polyadenylation, adapter ligation, reverse-transcription and miR-Amp reactions using the TaqMan™ Advanced miRNA cDNA Synthesis Kit (A28007, Thermo Fisher Scientific, Waltham, Massachusetts, US) following manufacturer’s instructions. Reactions will be performed on the standard thermocycler BioRad. The cDNA will be diluted, and real-time PCR runs for miRNA analysis will be performed using the Taqman Fast Advanced Mastermix for qPCR (4,444,964, Thermo Fisher Scientific, Waltham, Massachusetts, US) on QuantStudio™ 7 Flex Real-Time PCR System (Thermo Fisher Scientific, Waltham, Massachusetts, US).

Using TaqMan® Assays for miR-27a-5p and miR-30a-3p (assays 002445 and 000416 respectively, Thermo Fisher Scientific, Waltham, Massachusetts, US) their respective expressions will be calculated by the 2^−ΔΔCt^ method by using endogenous miRNA, one of RNU48, RNU44, U47, or RNU6B (Thermo Fisher Scientific, Waltham, Massachusetts, US) will be used as the reference genes. The ratio of miR-27a-5p/miR-30a-3p expression will be calculated. The ratio of these two miRNAs has previously been reported to differentiate concussed and non-concussed individuals; concentrations of miR-27a-5p and miR-30a-3p differentiated 75 concussed individuals from 97 non-concussed individuals with 82.4% sensitivity and 73.3% specificity. The levels of miR-27a-5p/miR-30a-3p were lower among concussed individuals and importantly showed no effect of acute or chronic exercise. These miRNAs showed similar accuracy for both sport and non-sport related concussion.

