## Discussion

There is a lack of female specific sports science and biomedical research. [20, 60–65] Previous studies investigating candidate biomarkers for concussion have either been conducted in exclusively male cohorts or have not considered the influence that fluctuations in circulating sex hormones may have on the expression of salivary biomarkers. This protocol is important as it will help to determine whether females with a suspected concussion have similar salivary sncRNA expression to those reported in the literature for male athletes [35] and highlight any potential for false negative or positive results when considering salivary biomarkers as a diagnostic tool for females with suspected concussion. If this study confirms presence of sncRNAs in females with concussion, it will provide evidence of the potential of saliva sampling as an objective tool to aid in diagnosis of and confirmation of recovery from concussion. Findings will highlight whether expression and ratio of two sncRNAs may be associated with sex hormones in females and therefore whether this would be a feasible and reliable tool for routine clinical use in this cohort. Findings will also highlight how different hormone profiles may be associated with concussion symptom severity and duration in females.

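### The ratio ANOVA fits Aim 2 but cannot by itself support the broader promised conclusion that hormones do or do not influence sncRNA expression

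*Protocol article*

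**What the plan says.** **Aim and analysis.** In the protocol article, the Aim section words Aim 2 as to "examine whether the ratio of sncRNAs in saliva differ across groups categorised by their hormone profiles at the point of concussion injury". The Data analysis section assigns it one test: "Aim 2 will apply an ANOVA to compare the ratios of miR-27a-5p/miR-30a-3p expression, across these five groups". It adds that "Model-estimated means and pairwise contrasts between groups will also be computed", with no further saliva outcome named.

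**Laboratory section.** Under sncRNA (miRNA) expression analysis, each miRNA's expression is obtained by the 2^−ΔΔCt method against one of four candidate reference genes, and then "The ratio of miR-27a-5p/miR-30a-3p expression will be calculated". The reason given for using the ratio is diagnostic: "The ratio of these two miRNAs has previously been reported to differentiate concussed and non-concussed individuals".

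**Promised conclusions.** The Discussion paragraph of the Abstract states: "Findings will determine whether expression of sncRNAs is influenced by steroid hormones in females". The main Discussion states: "Findings will highlight whether expression and ratio of two sncRNAs may be associated with sex hormones in females". The second sentence treats expression and ratio as two separate quantities.

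**The concern.** Aim 2 and its ANOVA agree with each other. The gap lies between that analysis and the two statements of what the findings will show. A ratio of two expression levels answers whether their balance differs by hormone profile. It does not answer whether either level differs.

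Two things are at stake. A null ratio result is compatible with a large hormone effect on both miRNAs, so it cannot support a statement that expression is unaffected. A positive ratio result does not tell the reader whether miR-27a-5p, miR-30a-3p or both moved. The Abstract links the expression finding to a possible need for sex-specific interpretation of these markers, so the distinction matters for how the results are used.

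**Working it through.** **The plan's own figures.** None is given for Aim 2. The numbers 30 and 38 come from the Aim 1 calculation (Sample size calculation) and reproduce with a two-sided 5% test: (1.960 + 0.842)² / (0.9 × (1 − 0.2) × 1.5² × 0.4055²) = 29.5, so 30; and 30 / 0.8 = 37.5, so 38. They are used below only as sample sizes.

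**Step 1: algebra (no assumptions on SD).** With one reference gene for both miRNAs and calibrator constants k:

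- log2 E(27a) = −(Ct27a − Ctref − k27a)
- log2 E(30a) = −(Ct30a − Ctref − k30a)
- log2 ratio = Ct30a − Ct27a + (k27a − k30a)

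The reference gene drops out. So does any common effect: if a hormone profile multiplies both miRNAs by c, then (c × E(27a)) / (c × E(30a)) is unchanged for every c. The ratio ANOVA then rejects only at its type I error rate, at any sample size.

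**Step 2: what decides power otherwise.** Let the log2 shifts be d27 and d30, the within-group SD be 1 for each miRNA, and their correlation be ρ. The ratio shifts by d27 − d30 and has SD √(2(1 − ρ)), which is 1.18 / 1.00 / 0.89 / 0.63 at ρ = 0.3 / 0.5 / 0.6 / 0.8.

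- Shifts 1.5 and 1.0: the standardised ratio shift is 0.5/1.18 = 0.42, 0.5/0.89 = 0.56 and 0.5/0.63 = 0.79 at ρ = 0.3, 0.6 and 0.8. The single miRNAs have 1.5 and 1.0.
- Shifts 1.5 and 0: the standardised ratio shift is 1.5/1.18 = 1.27, 1.5/1.00 = 1.50, 1.5/0.89 = 1.68 and 1.5/0.63 = 2.37. The ratio equals the single-miRNA test at ρ = 0.5 and beats it above that.

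**Step 3: simulation.** Assumed, and not in the article: log2 SD 1; 38 women in groups of 7/7/8/8/8; group shifts in the proportion 0 / 0.5 / 1 / 0 / 0 of the maximum shown; alpha 0.05; 20,000 runs per setting.

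| Maximum shift (27a, 30a) | Log-ratio ANOVA rejects, ρ = 0.3 / 0.6 / 0.8 | Single-miRNA ANOVA rejects (27a, 30a) |
|---|---|---|
| +1.5, +1.5 | 5% / 5% / 5% | 81%, 81% |
| +1.5, +1.0 | 10% / 15% / 28% | 81%, 43% |
| +1.5, 0 | 65% / 90% / 99.7% | 81%, 5% |
| +0.75, −0.75 | as the row above, because the ratio shift is again 1.5 | about 25% each |

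At ρ = 0.5 with one miRNA moving, the ratio rejects 81%, the same as the single-miRNA test. With 30 women (five groups of 6), the equal-shift row becomes 5% for the ratio against 66% for each miRNA.

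**Step 4: a different shift pattern.** With two of five groups shifted equally by 1.5 SD in both miRNAs, the log ratio again rejects about 5%, against about 85% (30 women) and 93% (38 women) for each miRNA. Analysing the untransformed ratio does not help: across the equal-shift settings run with this pattern it rejected 3.4% to 4.7%.

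**The case against.** The strongest reply is that the analysis does what its aim asks. Aim 2 is about the ratio, the ratio has a stated diagnostic rationale, and for a marker that is read as a ratio, a common shift that leaves it unchanged correctly means that the marker is unaffected. Cancelling the reference gene is also a practical advantage. All of this stands, and it is why the ratio ANOVA should stay.

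It can also be said that same-direction shifts are the case least favourable to a ratio. That stands too: when one miRNA moves alone at moderate or high correlation, or the two move apart, the ratio does as well or better. A reader might infer that the ratio is generally the weaker test; the table shows that it is not, and the article gives no reason to expect a parallel shift.

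A reader might further infer that a null ratio will be reported as no hormone effect on expression. The article nowhere says so. That error would arise only if the Abstract's conclusion were drawn from this ANOVA alone. Nor does the article exclude secondary analyses of each miRNA, since it condenses a fuller protocol and a statistical analysis plan may exist.

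What remains is that the article maps a specific test to each aim, makes an explicit promise about expression in two places, and names no analysis that could deliver it.

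**Conclusion.** The point holds as a mismatch between the named analysis and the promised conclusions, not as an error in the Aim 2 test. The ratio ANOVA cannot support a conclusion on expression: an equal fold change is invisible to it (about 5% rejection at any sample size), same-direction unequal changes are attenuated in the settings run (10% to 28% against 81% for the more affected miRNA), and a positive result does not show which miRNA moved.

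The cancellation is algebraic and needs no assumption beyond a shared reference gene. Every power figure depends on an assumed SD, correlation, group split and shift pattern, and the ranking reverses under other patterns. Severity is minor: Aim 2 is not the primary aim, and the remedy uses values already planned.

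**What to change.** 1. Keep the ratio ANOVA as the Aim 2 analysis.
2. Add the same five-group ANOVA on log2 expression of miR-27a-5p and of miR-30a-3p, labelled as two secondary analyses, with estimates and confidence intervals for the group differences.
3. Choose the reference gene from the four listed before the expression data are linked to hormone profile, and check that its Ct does not differ by profile. It cancels in the ratio but not in single-miRNA expression.
4. Draw any conclusion on expression from these analyses, and state that a null ratio will not be read as absence of hormone influence on expression.

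If the sponsor prefers not to add them, limit the conclusions in the Abstract and the Discussion to the ratio.

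**Cost.** No new samples or participants are needed, because the laboratory section already produces both expression values. The downside is two further tests in a sample that the limitations section already calls small for the number of variables, and dependence on a stable reference gene. The alternative costs only a change of wording.
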